## **6.2 Viral Shedding Assessment**

In order to reduce the possibility of transmission, volunteers will be housed in an isolation facility for 9 days following receipt of the vaccine (Days -2 to 9). Based on prior studies with other oral replicating adenovirus vectors, it is believed that maximum viral shedding will occur approximately 7 days following administration of the rcAd26.MOS1.HIV-Env vaccine. Given the 100-fold reduced replicative capacity of the vaccine compared to wild type virus and the limits of how long volunteers can reasonably be expected to stay in an isolation unit, the 9 day period was deemed appropriate. Within the facility, volunteers will reside alone in a hospital-style room with its own shower and toilet; volunteers will not be allowed to leave his or her room following immunization for the duration of the isolation period and can receive no visitors. Clinical staff will use contact precautions (gloves and disposable gown) when in physical contact with volunteers and/or in the volunteers' room; no other staff will enter the volunteers' room. Upon discharge from the isolation unit, instructions will be provided to each volunteer regarding methods to limit the possibility of transmission. Rectal and throat swabs will be assessed for rcAd26.MOS1.HIV-Env by PCR as outlined in Schedule of Procedures (Section 18.5); if a rectal or throat swab is positive by PCR, then adenovirus culture will also be performed. Plasma adenovirus PCR will be performed on day 7 but results will not be available prior to discharge from the isolation unit; if plasma adenovirus PCR is positive by PCR, then adenovirus culture will also be performed.

Real-time (rt)PCR analysis will be performed for both the Ad26 vector and the Env insert to allow for quantitation of vector and insert and to evaluate the stability of the vaccine. If the PCR is positive, adenovirus cultures will also be performed to evaluate for the presence of infectious virus and to allow eventual correlation of PCR and culture results; PCR will be performed on positive cultures to confirm that the virus is rcAd26.MOS1.HIV-Env.

All shedding samples will be frozen, and all PCR and cultures will be performed at CVVR. Investigators and study clinicians will be blinded to adenovirus PCR and culture results, but a single individual on the study team will be unblinded to gain access to the results from day 28. If a volunteer's adenovirus PCR remains positive at day 28, weekly adenovirus PCR will be performed until the PCR is negative.

## **6.3 Immunogenicity Assessment**

Blood samples will be obtained at various time points after immunization (Section 18.5). These will be assayed for the magnitude of antibody binding to HIV-1 Env as quantified by enzyme-linked immunosorbent assay (ELISA), the magnitude of neutralizing antibodies against HIV-1 as quantified by virus neutralization assay, and the magnitude of HIV-1-specific T lymphocyte responses as quantified by interferon-gamma (IFN- $\gamma$ ) enzyme-linked immunospot assay (ELISPOT). Additional studies may include measurement of Ad26-specific antibodies, ADCC and ADCVI, epitope mapping, and mucosal immune responses. Laboratory studies will be conducted in the labs of Drs.

[name], [name], and [name] at the CVVR. Additionally, rectal mucosal secretions will be collected with rectal wicks for evaluation of potential mucosal immunity to HIV-1 Env and Ad26 (this procedure will be optional for volunteers). Studies may include measurement of Ad26 and HIV-1-specific antibodies by ELISA, and antibody epitope mapping to Env peptides by linear peptide microarray.

## 6.4 Monitoring

The Safety Monitoring Committee (SMC) and Protocol Safety Review Team (PSRT) will review the safety data through Day 9 post vaccination for all volunteers in each dosage group. In addition, the SMC will oversee the study as outlined in Section 10.9, and will advise the PSRT as needed. *Ad-hoc* safety review may be specifically requested by the Sponsor, PaxVax, Batavia, the Principal Investigators, Ethics Committees, Regulatory Authorities, PSRT or SMC.

## 6.5 Household Contacts

Study volunteers will be required to live alone or have no more than 2 adult household contacts, as detailed in the inclusion criteria. A household contact is defined as an individual who shares the same residence as the volunteer. Household contacts will provide informed consent and will be enrolled in the study as a household contact. After a volunteer has been discharged from the isolation facility, the volunteer's household contacts will be contacted on a weekly basis for a period of 2 weeks to assess for the presence of illness that may be related to transmission of rcAd26.MOS1.HIV-Env. If such illness is suspected, the household contact will be seen in clinic to further assess if Ad26 was the cause of illness. This may include blood tests as well as rectal or throat swabs for PCR and culture, depending on the type of illness present. Household contacts will be consented and continue to be followed for a period of 8 months, as detailed in the Schedule of Procedures for household contacts in Section 18.6.

## 6.6 Randomization Procedures and Enrollment

Volunteers will be enrolled in the study after ascertainment by one of the study investigators that all of the inclusion and none of the exclusion criteria have been met. Once confirmation of eligibility for the trial has been performed, the volunteer will be randomized. Randomized treatment assignments will be generated by the Data Management Center (DMC). After successful randomization, an allocation number is provided. The DMC will create the randomization table and the sponsor will monitor the implementation of this process. The allocation number is referenced against a confidential list provided to an unblinded on-site pharmacist to determine the assignment/treatment allocation.

The 6 volunteers in each group will be randomized in a ratio of 5 vaccinees to 1 placebo recipient. The study preparation will be provided to the study nurses for oral administration under a coded, masked identification. For the  $10^8$  and  $10^{10}$  doses, volunteers will receive a single capsule, while the doses at  $10^9$  and  $10^{11}$  will consist of 10 capsules of  $10^8$  or  $10^{10}$ , respectively. For each group, placebo recipients will receive the same number of capsules as those receiving the active treatment. For the  $10^8$  and  $10^9$  doses, the placebo and vaccine preparations will be indistinguishable in the preparation provided for volunteers. For the  $10^{10}$  and  $10^{11}$  doses, the placebo capsules will be

smaller than the vaccine capsules (size 3 vs. size 1), but will otherwise be indistinguishable.

## **6.7 Method of Blinding and Unblinding**

The volunteers, clinical staff, investigator, and sponsor personnel will be blinded to treatment allocation throughout the study. A single member of the study team will have unblinded access to Ad26 shedding cultures results from day 28 after vaccination. The pharmacist with primary responsibility for vaccine dispensing will not be blinded to the treatment and will maintain the randomization code and complete assignments of volunteers according to the randomization allocation. For the  $10^{10}$  and  $10^{11}$  doses, a single member of the clinical staff with primary responsibility for vaccine administration to volunteers will not be blinded to the treatment, given that the vaccine and placebo capsules are different sizes; this staff member will not participate in clinical management or data analysis. For these doses, the volunteers will remain blinded as they will be isolated from one another. Routine unblinding of treatment allocations may occur only after all volunteers have had their last study visit and the database is locked.

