### 6.1 Safety Assessment

On Days 0-9 post vaccination of the isolation portion of the study, a study clinician (MD, NP, and/or nurse) will assess the volunteers with a directed medical history and abbreviated physical examination (once daily, noting any medication use), review the volunteer's reactogenicity diary card (once daily), and check vital signs (twice daily). Any unsolicited adverse events observed or reported at any time of day will also be noted.

After the completion of the isolation portion of the study, adverse events will be assessed at follow up visits, as detailed in the Schedule of Procedures (Section 18.5). Hematology and blood chemistries will also be assessed as detailed in the Schedule of Procedures.

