#### **8.1.1 rcAd26.MOS1.HIV-Env**

rcAd26.MOS1.HIV-Env vaccine is formulated as Acryl-EZE enteric-coated capsules for oral administration. The  $10^8$  and  $10^9$  doses will be administered in size 3 capsules. The  $10^{10}$  and  $10^{11}$  doses will be administered in larger size 1 capsules.

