#### **8.1.2 Placebo**

The placebo is formulated as Acryl-EZE enteric-coated capsules for oral administration. Capsules will be size 3.

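### In Groups 3 and 4 the placebo and vaccine capsules differ in size, and isolating volunteers from one another does not by itself secure the blind

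*Protocol*

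**What the plan says.** Section 8.1.1 states that the 10^10 and 10^11 vp "doses will be administered in larger size 1 capsules". Section 8.1.2 says of the placebo: "Capsules will be size 3". Section 6.6 acknowledges the result: at these two dose levels the placebo capsules are "smaller than the vaccine capsules (size 3 vs. size 1), but will otherwise be indistinguishable". The number of capsules is matched: "For each group, placebo recipients will receive the same number of capsules as those receiving the active treatment". Allocation is fixed within each group: "The 6 volunteers in each group will be randomized in a ratio of 5 vaccinees to 1 placebo recipient".

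Section 6.7 opens by declaring volunteers, clinical staff, investigator and sponsor personnel blinded for the whole study. For the two highest doses it then assigns the giving of the product to one clinical staff member, who is unblinded because of the size difference and is kept out of clinical management and of the data analysis. For the volunteers the only reason offered is: "For these doses, the volunteers will remain blinded as they will be isolated from one another".

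Two other sections matter here. Section 6.1 has a study clinician "assess the volunteers with a directed medical history and abbreviated physical examination" once daily on Days 0 to 9, together with a daily diary review. Section 6.2 describes the isolation: "volunteers will not be allowed to leave his or her room following immunization for the duration of the isolation period", with no visitors. Section 8.2.3 has the volunteer swallow the capsules with water and describes no concealment.

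**The concern.** Section 6.7 itself treats capsule size as enough to reveal the arm, since that is why the administrator is declared unblinded. The volunteer handles the same capsules. Keeping volunteers apart removes one route by which size becomes informative, namely comparison with another volunteer. It leaves open the route from volunteer to assessor, which needs no contact between volunteers at all.

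The primary objective is safety and tolerability. It rests on solicited symptoms that volunteers report and on investigators' judgements of relatedness, and both can shift if the arm is known. Under section 9.8.3, relatedness also helps decide whether a pause rule applies. Section 6 gives reduced observer bias as a purpose of the blinded design, and section 12.3 says the placebo recipients are there partly for blinding. In Groups 3 and 4 that purpose is not secured by the reason given.

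**Working it through.** The protocol gives no figure for the security of the blind. Its one statistical figure, the zero-event upper limits in section 12.3, reproduces (1 − 0.025^(1/4) = 60.2%; 1 − 0.025^(1/5) = 52.2%), but nothing below rests on it.

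**Inputs**
- Vaccine size 1, placebo size 3, at 10^10 and 10^11 vp (6.6, 8.1.1, 8.1.2).
- Equal capsule number within a group: one in Group 3, ten in Group 4 (6.6).
- Six volunteers per group, exactly one on placebo (6.6, Table 1).
- Isolation from Day -2 through Day 9 (section 6, Table 1).
- Adverse events collected to Day 112 (10.1.2.2). Endpoints include solicited reactions to Day 9 and related unsolicited events to 4 weeks (12.2).

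**Who is affected.** 2 groups × 6 = 12 of 24 volunteers: 2 × 5 = 10 of 20 vaccinees and 2 × 1 = 2 of 4 placebo recipients.

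**Which routes are closed**
- *Administrator to assessor:* largely closed by the dedicated administrator in 6.7.
- *Volunteer to volunteer:* closed by isolation to Day 9 and open afterwards. That leaves 28 − 9 = 19 days of the 4-week endpoint and 112 − 9 = 103 days of adverse event collection outside it.
- *Volunteer to assessor:* not closed. Clinicians take a history and review the diary daily, and the size code is printed in their protocol. Nothing in the text shown hides the capsules or asks volunteers not to describe them.

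**What a disclosure reveals.** Take an assessor who knows the size code and a remark that identifies the size.
- Before any remark, each volunteer has probability 1/6 of being on placebo.
- After one remark, that volunteer's arm is known with certainty.
- If the speaker is the placebo recipient (probability 1/6 for a random speaker), the other five must be vaccinees and all six allocations are known.
- If the speaker is a vaccinee (probability 5/6), the placebo recipient is one of the other five, so each of them moves from 1/6 to 1/5.

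For k volunteers disclosing at random, the chance that the whole group is known is k/6 for k up to 4, and 1 for k of 5 or more, because the sixth then follows by elimination:
- k = 1: 1/6
- k = 2: 1/3
- k = 3: 1/2
- k = 4: 2/3
- k = 5 or 6: 1

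**The case against.** The case for leaving the text alone has real substance.

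- **The volunteer's own blind.** A volunteer sees one capsule size and has nothing to compare it with. Size is informative only to someone who knows the code, and nothing shown says volunteers are told it (the consent pages are not available). This stands: the mismatch does not in itself unblind a volunteer.
- **Staff.** The dedicated administrator is a genuine safeguard. This stands, but it does not cover what a volunteer says to someone else.
- **Timing.** Solicited reactions are recorded on Days 0 to 9, in single rooms without visitors, so contact after discharge cannot alter diary entries already made. This stands for contact between volunteers. It does not answer a remark to an assessor during isolation, nor does it cover later unsolicited events.
- **Pausing and escalation.** Seven common reactogenicity symptoms are excluded from the Grade 3 or 4 pause rule, and the Safety Monitoring Committee may see data by arm (10.9). This limits the consequence. Investigator causality for other events remains exposed.
- **Descriptive trial.** There is no hypothesis test and only one placebo recipient per group, so no formal comparison is at risk. This also limits the consequence.
- **Other documents.** Section 8.1 places detailed product instructions in the Study Operations Manual, which may already describe concealed dosing. If so, the protocol should say that this protects the blind, instead of relying on isolation.

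A reader might infer that the size difference necessarily unblinds the volunteers and the assessors, or that any single remark reveals the whole group. The documents do not support either reading. The first needs knowledge of the size code, or a disclosure. The second holds only when the speaker is the placebo recipient.

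**Conclusion.** The point holds as a conditional risk. In Groups 3 and 4, half the trial and its two highest doses, the blind depends on volunteers not knowing or reporting capsule size, and the reason given in 6.7 does not secure that. One identifying remark settles the speaker's arm. With probability 1/6 it settles the whole group; otherwise it changes little for the other five (1/6 to 1/5).

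These figures assume that the assessor knows the code, that the remark truly identifies the size, and that speakers are a random selection. The documents give no basis for estimating how often such remarks would occur, so the expected bias cannot be quantified. The exposure is mainly to reactogenicity reports and to investigator causality judgements, not to the committee's escalation decision, since the committee may look at data by arm.

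The text also needs reconciling. The opening sentence of 6.7 has clinical staff blinded throughout, yet the same section names an unblinded clinical staff member. Section 6.6 has study nurses receiving masked product, with no exception for these two groups.

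**What to change.** In 6.7 and 8.2.3, replace the isolation rationale for Groups 3 and 4 with these provisions:
- Present the capsules concealed, for example in an opaque container tipped to the mouth, so that neither the volunteer nor blinded staff see them.
- Instruct volunteers and assessors not to discuss capsule size. Capsule number needs no such instruction, because it is the same in both arms.
- State that the unblinded administrator takes no part in the 30-minute post-dose observation (10.1.2.3) or in any adverse event assessment. The present exclusion from clinical management implies this but does not say so.
- Amend 6.6 and the opening sentence of 6.7 to name the administrator as the exception.

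The cost is protocol wording, a short instruction, and slightly more handling at dosing, chiefly for the ten-capsule dose. Concealment is not complete, because a volunteer may still sense capsule size when swallowing.

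A size 1 placebo matched to the vaccine would be preferable if supply allows, and would also remove the need for an unblinded administrator. The quantity is small: 1 recipient × 1 capsule + 1 recipient × 10 capsules = 11 capsules before spares. The documents give no information on placebo manufacture, so its cost and feasibility are for the sponsor to judge. No change to dose, schedule or sample size is involved.

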## 7 STUDY POPULATION

The study population will include healthy men or women aged 18-50 years old who are able and willing to provide written informed consent. Because of the possibility of transmission with the use of a replication competent vaccine, volunteers will reside alone or with no more than 2 adults, who must consent to participate in the study as a Household Contact. Volunteers will be enrolled in the study once eligibility criteria are met.

### 7.1 Volunteer Inclusion Criteria

1. Age 18-50 years old.
2. Ability and willingness to provide informed consent.
3. Assessment of understanding: completion of a questionnaire prior to first screening procedure; verbally demonstrate understanding of all questionnaire items answered incorrectly.
4. Available for the duration of the trial, including willingness to be kept in an isolation facility for Days -2 to 9.
5. From Day 10 through 4 months following vaccination must reside alone or with no more than 2 adults (age 18-60) and no minors under age 18 who are willing to consent to participate in the study as a Household Contact. A Household Contact is defined as an individual who shares the same residence as the volunteer.
6. Good general health as shown by medical history, physical exam, and screening laboratory tests.
7. The following laboratory parameters:
  - a. Hematology
    - Hemoglobin  $\geq 11.0$  g/dL for women;  $\geq 12.5$  g/dL for men
    - Absolute Neutrophil Count (ANC):  $\geq 1000/\text{mm}^3$
    - Absolute Lymphocyte Count (ALC):  $\geq 500/\text{mm}^3$
    - Platelets: 125,000 to 550,000/ $\text{mm}^3$
  - b. Chemistry
    - Creatinine:  $< 1.1 \times$  upper limit of normal (ULN)
    - AST:  $< 1.25 \times$  ULN
    - ALT:  $< 1.25 \times$  ULN
  - c. Normal urinalysis
    - Negative urine glucose
    - Negative or trace urine protein
    - Negative or trace urine hemoglobin (if trace hemoglobin is present on dipstick, a microscopic urinalysis within institutional range)
8. Willing to undergo HIV testing and receive HIV test results, and willing to receive risk reduction counseling

9. All female volunteers must be willing to undergo urine beta human chorionic gonadotropin pregnancy tests at time points indicated in the Schedule of Procedures (Section 18.4) and must test negative prior to vaccination
10. All sexually active males (unless anatomically sterile) must be willing to use an effective method of contraception (such as consistent condom use) from the day of vaccination until at least 4 months after vaccination
11. If a woman of child-bearing potential, committed to use an effective method of contraception when sexually active with men for 4 months following the receipt of vaccine, including:
  - a. Condoms (male or female) with or without spermicide
  - b. Diaphragm or cervical cap with spermicide
  - c. Intrauterine device
  - d. Hormonal contraception
  - e. Successful vasectomy in the male partner (considered successful if a woman reports that a male partner has [1] documentation of azoospermia by microscopy, or [2] a vasectomy more than 2 years ago with no resultant pregnancy despite sexual activity post-vasectomy)
  - f. Not be of reproductive potential, such as having undergone hysterectomy, bilateral oophorectomy, or tubal ligation
12. Willing to forgo donations of blood or any other tissues during the study and, for those who test HIV positive due to trial vaccination (vaccine-induced HIV seroreactivity), until the anti-HIV antibody titers become undetectable
13. Low risk for HIV infection (see Section 18.2) and willing to maintain low-risk behavior for the trial duration

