## 10 SAFETY ASSESSMENTS

### 10.1 Adverse events

#### 10.1.1 Definitions

##### Adverse events

An AE is any untoward medical occurrence in a patient or volunteer, and does not necessarily have a causal relationship with a medical treatment. This includes any noxious, pathological, or unintended change in anatomical, physiological, or metabolic functions, as indicated by physical signs, symptoms, and/or laboratory-detected changes. These might occur in any phase of the clinical study whether associated with the study vaccine or not. This includes exacerbations of pre-existing conditions or events, intercurrent illness, or vaccine or drug interactions. Anticipated day-to-day fluctuations of pre-existing conditions that do not represent a clinically significant exacerbation are not considered AEs. Discrete episodes of chronic conditions occurring during a study period should be reported as AEs in order to assess changes in frequency or severity.

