#### **10.1.2.2 Documentation of adverse events**

All AEs will be collected on case report forms (CRFs) from the signing of the ICF until Study Day 112. SAEs will be collected through Study Day 365.

AEs and SAEs should be documented in terms of signs and symptoms observed by the investigator or reported by the volunteers. Whenever possible, a medical diagnosis should be made. The nature of each event, date and (where appropriate) time of onset, outcome, severity, and causal relationship should be established. Details of any symptomatic/corrective treatment should be recorded on the appropriate page of the CRF.

Hospitalization for routine clinical procedures (or other reason) that is not the result of an AE, are not considered AEs but will be recorded on the AE page of the CRF ('Hospitalization, Not an AE'). The same applies for hospitalization for elective procedures related to a pre-existing condition that did not increase in severity or frequency during the study. If hospitalization was planned before administration of the study vaccine, it will be documented in the Medical History page of the CRF (see below).

The following events will be documented in the Medical History page of the CRF:

- Pre-existing conditions or signs and/or symptoms present in a volunteer before study start. This includes conditions that were not recognized at study entry but later during the study period.
- Hospitalization arising from a pre-existing condition and planned before the administration of the vaccine.

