### **10.3.1 Severity of adverse events**

All AE and lab data will be coded for severity using the DAIDS Table for Grading the Severity of Adult and Pediatric Adverse Events (DAIDS AE Grading Table), **Version 1.0 dated December 2004** (Clarification, August 2009) included in Section 18.1, and also located on the website: <http://rsc.tech-res.com/safetyandpharmacovigilance/>.

For AEs not identified in the grading table (e.g. diagnosis of HIV infection), the following guidelines will be applied:

|                                     |         |                                                                                                                                                                       |
|-------------------------------------|---------|-----------------------------------------------------------------------------------------------------------------------------------------------------------------------|
| Mild                         | Grade 1 | Symptoms causing no or minimal interference with usual social and functional activities                                                                               |
| Moderate                     | Grade 2 | Symptoms causing greater than minimal interference with usual social and functional activities                                                                        |
| Severe                       | Grade 3 | Symptoms causing inability to perform usual social and functional activities                                                                                          |
| Potentially life-threatening | Grade 4 | Symptoms causing inability to perform basic self-care functions OR medical or operative intervention indicated to prevent permanent impairment, persistent disability |
| Fatal                        | Grade 5 | For any AE where the outcome is death, the severity of the AE is classified as Grade 5                                                                                |

The clinical research site team will ascertain accurate recording of all AEs during the study. AE CRFs will be completed by the clinical research site staff on a daily basis as the data become available from the isolation unit, clinic or laboratory.

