### **10.6 Routine safety laboratory**

Samples for routine safety laboratory parameters will be collected at the time points specified in Section 18.7.

The following routine safety laboratory parameters will be determined:

- **Serum chemistry:** AST, ALT, and Creatinine
- **Complete blood count:** hemoglobin, hematocrit, white blood cells (WBC), WBC differentiation, red blood cell count (RBC), and platelet count

Laboratory values will be graded according to the DAIDS toxicity scale (Section 18.1) and, if clinically significant, reported as AEs.

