### **12.2 Endpoints**

Safety and tolerability:

- Any adverse events within 4 months following vaccination (SAEs within 12 months following vaccination)
- Moderate or greater unsolicited adverse events related to study product (i.e., suspected adverse reactions) within 4 weeks post-vaccination
- Moderate or greater solicited reactions within 9 days post-vaccination

Shedding:

- Proportion (95% CI) of volunteers per dose group with positive responses and mean response per group with 95% CI.
  - Rectal/oral shedding: real-time PCR for rcAd26.MOS1.HIV-Env at 1, 2, 3, 4, 5, 6, 7, 8, 9, 12, 17, 21, 7, 12, 21, and 28 days after vaccination.

Immunogenicity:

- Proportion (95% CI) of volunteers per dose group with positive responses and mean response (e.g. GMT) per group with 95% CI.
  - Cellular immunogenicity: Env-specific ELISPOT responses at 4 weeks after vaccination.
  - Humoral immunogenicity: Env-specific binding antibody titers at 4 weeks after vaccination.

- Durability of responses: immunogenicity assays at 4, 8 and 12 months after vaccination.

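### The lymphocyte entry limit does not match the trial's own toxicity scale: it admits counts already graded 1 or 2 and sits one cell above Grade 3

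*Protocol*

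**What the plan says.** Section 7.1, item 7, lists laboratory limits for entry. The line "Absolute Lymphocyte Count (ALC" requires at least 500/mm³, the line "Absolute Neutrophil Count (ANC" at least 1,000/mm³, and the platelet line reads "Platelets: 125,000 to 550,000". Limits for hemoglobin, creatinine, AST and ALT follow the same format.

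Section 10.3.1 states: "All AE and lab data will be coded for severity using the DAIDS Table". That table is reproduced in Section 18.1, and its lymphocyte cut-offs are absolute counts.

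Several passages govern what happens to a graded value:

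- Section 10.6: "Laboratory values will be graded according to the DAIDS toxicity scale (Section 18.1) and, if clinically significant, reported as AEs".
- Section 10.1.1: "Anticipated day-to-day fluctuations of pre-existing conditions that do not represent a clinically significant exacerbation are not considered AEs".
- Section 10.1.2.2 sends to the Medical History page "Pre-existing conditions or signs and/or symptoms present in a volunteer before study start".
- Section 12.2 lists among the safety endpoints "Moderate or greater unsolicited adverse events related to study product (i.e., suspected adverse reactions) within 4 weeks post-vaccination".
- Table 2 in Section 9.8.3 acts on related Grade 3 or 4 AEs. Its notes ask for a probable or definite relation and for a repeat draw when a laboratory value stands alone.

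**The concern.** Most of the entry limits stop where Grade 1 begins, so a volunteer starts with no graded abnormality and any later grade is new. The lymphocyte limit breaks that pattern by more than one grade. A count admitted at entry can appear in post-dose laboratory data as Grade 2 without any change, and ordinary variation near the floor can turn it into Grade 3. With five vaccinees per dose group, one such volunteer is 1/5 = 20% of the group. In a first-in-human study of a replicating vector, a low lymphocyte count after dosing will draw attention. The reader of the safety data should be able to tell whether it was there before.

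**Working it through.** **Step 1. Entry limits (Section 7.1 item 7) beside the grades (Section 18.1).**

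| Analyte | Entry limit | Grade 1 | Worst grade admitted |
|---|---|---|---|
| Lymphocytes (/mm³) | ≥ 500 | 600–650 | Grade 2 (500–599) |
| Neutrophils (/mm³) | ≥ 1,000 | 1,000–1,300 | Grade 1 |
| Platelets (/mm³) | ≥ 125,000 | 100,000–124,999 | none |
| Hemoglobin (g/dL) | ≥ 11.0 women, ≥ 12.5 men | 10.0–10.9 | none |
| AST, ALT | < 1.25 × ULN | 1.25–2.5 × ULN | none |
| Creatinine | < 1.1 × ULN | 1.1–1.3 × ULN | none |

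Lymphocytes are the only one of these analytes whose limit admits Grade 2. Mapping single counts: 499 is Grade 3 (excluded); 500, 550 and 599 are Grade 2 (eligible); 600 and 650 are Grade 1 (eligible); 651 is ungraded (eligible).

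**Step 2. Fall from the entry floor needed to reach Grade 3**, as (floor − highest Grade 3 value) / floor:

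- Lymphocytes: (500 − 499)/500 = 0.2%
- Neutrophils: (1,000 − 749)/1,000 = 25.1%
- Hemoglobin, women: (11.0 − 8.9)/11.0 = 19.1%; men: (12.5 − 8.9)/12.5 = 28.8%
- Platelets: (125,000 − 49,999)/125,000 = 60.0%

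**Step 3. How easily chance produces that fall (illustration).** The protocol gives no within-person variability, so a coefficient of variation (CV) of 5–20% is assumed. Later counts are taken as normal around the volunteer's usual count m, and P(count < 500) = Φ((499.5 − m)/(CV × m)). For m = 550:

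- CV 5%: Φ(−50.5/27.5) = 3.3%
- CV 20%: Φ(−50.5/110) = 32.3%

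Per draw, with no vaccine effect:

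| Usual count | CV 5% | CV 20% |
|---|---|---|
| 500 | 49.2% | 49.8% |
| 550 | 3.3% | 32.3% |
| 599 | 0.0% | 20.3% |
| 651 | 0.0% | 12.2% |
| 1,000 | 0.0% | 0.6% |

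Section 18.5 schedules three post-dose blood counts in the AE collection period (Days 7, 17 and 112). If draws are independent, the chance of at least one Grade 3 value is 1 − (1 − p)³, which at m = 550 is 9.6% to 69.0%.

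These figures are conditional on the usual count. Someone who screens once at 550 may usually run higher, which lowers them. The documents do not say how many volunteers would have counts of 500–650.

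**Step 4. What a graded value must pass before it counts.**

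- To be an AE, it must be clinically significant (Section 10.6).
- To enter the moderate-or-greater unsolicited endpoint, it must be an AE and related to study product (Section 12.2).
- To reach the AE rows of Table 2, it must be a Grade 3 or 4 AE, judged probably or definitely related, and confirmed on repeat draw if isolated. A first such AE brings review by the safety team; a second occurrence pauses the study.

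An admitted entry count is at most Grade 2, so an unchanged one cannot meet those AE rows.

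**The case against.** A reader might infer that pre-existing low counts feed straight into the safety endpoints and the pause rule. The documents do not support that, for the reasons in Step 4. Sections 10.1.1 and 10.1.2.2 also keep fluctuation of pre-existing conditions out of the AE count and record such conditions as history. In addition, Section 10.3 reserves a probable relation for events that extraneous causes cannot explain, and a documented low screening count is such an explanation. This part of the objection stands.

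A reader might also extend the point to neutrophils. That does not hold either: the limit admits Grade 1 only, below any moderate-or-greater threshold, and Grade 3 needs a fall of about a quarter.

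Two further objections have weight. Entry limits need not mirror a grading table: Section 7.2 item 17 admits an undiagnosed volunteer with a systolic pressure of 140–149 mmHg, which Section 18.1 grades 1. And baseline-relative reporting is commonly left to the SAP, which is not available here, so its absence from the protocol is not a defect.

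The filters do not settle everything. Clinical significance and causality are judgments. Section 10.1.1 counts laboratory-detected changes as possible AEs, while the carve-outs speak of conditions, signs and symptoms and do not clearly cover a symptomless low count. The any-AE endpoint needs no relation, and Section 10.3 counts possibly related events as related in the final analyses. The repeat draw confirms a value but does not compare it with baseline.

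**Conclusion.** The mismatch between Section 7.1 item 7 and Section 18.1 is certain for lymphocytes: the limit admits Grades 1 and 2 and lies one cell/mm³ above Grade 3. Its consequence is modest. Graded laboratory data may show Grade 2 lymphopenia that predates dosing, and a trivial fall may produce a Grade 3 value that someone must attribute. It does not follow that admitted values become endpoint events or pause triggers by themselves. The chance figures rest on an assumed CV, a normal model and, over several draws, independence. The number of volunteers affected cannot be derived from the protocol. It is probably small, given 24 volunteers, the good-health criterion and the exclusion of immunodeficiency. Severity is low; the point is worth making because the correction is cheap.

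**What to change.** Reconcile the lymphocyte limit in Section 7.1 item 7 with the grades in Section 18.1, as the platelet, liver enzyme, creatinine and hemoglobin limits already are, so that volunteers do not enter with a count the trial grades as toxicity. If the lower limit is intended, give the reason. The clinical team should set the value.

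In Section 10.6 or 12.2, or in the SAP, state that post-dose laboratory grades are tabulated against the Day 0 value, for example as a shift from Day 0 grade. Section 18.5 already schedules a Day 0 blood count and chemistry; confirm that the sample is taken before dosing.

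Leave the Table 2 pause rules and the neutrophil limit as they are. Counting a value toward Table 2 only when it exceeds the Day 0 grade would narrow a safety rule, and a fall from 500 to 499 would still count.

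The cost is a few lines of text, no new sample, and possibly a few more screen failures. Alignment reduces chance Grade 3 values but does not abolish them: at a usual count of 651, just outside Grade 1, the illustration still gives 0.0–12.2% per draw, so the Day 0 comparison is useful in its own right.
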